### Supplementation

Following successful completion of the screening CPX, participants who meet the inclusion criteria will be randomly allocated in a double-blind fashion to determine the order of treatment (beetroot juice or placebo). A technical staff member of Victoria University, external to the project, will color code the beetroot juice bottles and provide a randomization sheet to the research team that has the conditions removed and replaced with colors.

Participants will consume three 70-ml bottles of beetroot juice (BEET IT shot, James White Drinks, Ipswich, UK) per day of either a nitrate-rich beetroot juice (16 mmol of nitrate/day total) or a nitrate-depleted placebo for 5 days before they commence testing. They will then continuously dose until they complete all 4 testing visits. There will be a 2-week washout period between the 2 rounds. As the half-life of nitrate is 5-8 hours, a 2-week washout period should be sufficient to minimize any possible residual effect of nitrate [45]. The order of testing visits will be kept consistent for each participant between the beetroot juice and placebo testing rounds. On testing days, patients will consume the first bottle of either beetroot juice or placebo 2.5 to 3 hours prior, as plasma nitrite concentration peaks within 2.5 to 3 hours postingestion [23,24]. To assess supplementation compliance, participants will maintain a dosing log and return all bottle caps to the research team.

The cumulative body of literature identifies that decreases in the oxygen cost of exercise and increases in power output and time to exhaustion were seen in studies using a minimum dose of 5.2 mmol nitrate for 6 days [22,25-27]. A longer dosing protocol (15 days) demonstrated that improvements in steady-state VO_2_ seen at day 5 were maintained but not increased at day 15 [46]. A previous clinical trial has demonstrated that an 18.1 mmol nitrate/day dose was feasible and safe for patients with peripheral arterial disease, whereas doses as high as 12.9 mmol nitrate/day have been used in the CHF population [40,47,48]. Thus, the dosing amount (16 mmol nitrate) and duration (minimum of 5 days before first testing session) for this study were selected to maximize the potential effects of the nitrate supplementation.

### Quality of Life and Health Status Questionnaires

In addition to the physiological measures attained, participants will be asked to complete a series of questionnaires through the study, including the Minnesota Living with Heart Failure Questionnaire (MLHFQ) to determine how their CHF has affected their life during the last month; the Subjective Exercise Experience Scale (SEES) to assess the effect of an acute exercise bout on positive well-being, psychological distress, and fatigue; and finally, they will complete a Physical Activity Questionnaire (PAQ) to confirm their current level of physical activity [49,50].

Participants will be asked to complete MLHFQ and PAQ a total of 2 times, once before commencing each testing round to ensure there is no change in how their CHF affects their daily life and how much they are exercising. MLHFQ has been previously validated for the use of the resulting physical, emotional, and total scores in patients with CHF [50]. Participants will be asked to complete SEES after every exercise test for the duration of the study, including the screening CPX. This 12-question scale was developed and validated as a 3-factor measure (positive well-being, psychological distress, and fatigue) of psychological response to exercise and has been previously validated [51].

### Maximal Cardiopulmonary Exercise Test Testing Visit

Participants will complete a 2-phase treadmill test identical to the screening CPX but with the addition of blood draws at rest and 10 min into recovery (to allow for postexercise blood volume stabilization) to quantify both resting plasma nitrate/nitrite as well as postexercise nitrate/nitrite changes.

Upon arrival for the testing visit, a catheter will be inserted into the antecubital vein of the participant to allow for repeated blood sampling. At this visit, 30 ml of blood will be collected in total. Following the resting blood draw, participants will be fitted with a 12-lead electrocardiograph to monitor their heart rhythms throughout the maximal test. Additionally, a near-infrared spectrometry (NIRS, PortaMon, Artinis Medical Systems B.V., The Netherlands) device will be placed on the skin above the gastrocnemius muscle of the participant. The NIRS system is noninvasive and provides an assessment of tissue oxygenation via the transmission of specific wavelengths of light (850 nm and 764 nm) that are absorbed by oxy- and deoxyhemoglobin, respectively [52]. A detection probe within the device measures the intensity of the received and transmitted light, which is communicated to a laptop via Bluetooth, and the corresponding software calculates the relative concentrations (and relative change) of oxygenated and deoxygenated hemoglobin within the muscle tissue. The device will be placed on the widest part of the medial head of the gastrocnemius, which is located by having the participant perform a short series of calf raises. A measuring tape will be used to identify the vertical point on the calf corresponding to the widest girth. A skinfold measurement will be taken at the selected site to ensure that the adipose tissue is less than 1.5 cm (typically the calf has less than 1 cm) [53]. The site will then be prepped with alcohol wipes (and shaving if appropriate), and the device will be affixed with micropore tape. Once the device is placed, vertical measurements are then taken from the top of the device to the bottom of the medial malleolus for reproducibility purposes on future tests. To ensure no light enters the NIRS device, a black plastic will be wrapped over the device and taped into place.

Additionally, a PhysioFlow (Physio Flow; Manatec Biomedical; Macheren, France) device will be used to estimate CO and the systemic vascular resistance index both at rest and during exercise. The device is a noninvasive hemodynamic monitor that provides real-time calculations of CO and various other parameters based on the morphological analysis of the bioelectrical impedance waveform. This device has been previously validated for measures of CO in healthy populations, but the studies in clinical populations thus far have been limited [54-57].

After 10 min of resting data collection, participants will be asked to complete a 2-step maximal treadmill CPX (as in the screening visit). Upon completion, the participant will be seated for recovery and at 10-min postcompletion will have a final 5 ml of blood drawn. Additionally, to allow for comparisons of the NIRS results to be made between subjects, a postexercise physiological calibration will be used to convert the relative concentration values to a normalized scale. For this, an occlusion cuff will be applied to the NIRS leg just above the knee, and the patients will undergo 5 min of ischemia. The baseline value for the scale will be the plateau of the oxygenated hemoglobin signal, whereas the signal response to postcuff release will provide a functional maximum for the normalized scale. All values obtained during the testing will then be expressed as a percentage value within these ranges [58].

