**Methods:**

Patients with chronic heart failure (15=HFpEF and 15=HFrEF) aged 40 to 85 years will be recruited. Following an initial screen cardiopulmonary exercise test, participants will be randomly allocated in a double-blind fashion to consume either a nitrate-rich beetroot juice (16 mmol nitrate/day) or a nitrate-depleted placebo (for 5 days). Participants will continue daily dosing until the completion of the 4 testing visits (maximal cardiopulmonary exercise test, submaximal exercise test with echocardiography, vascular function assessment, and vastus lateralis muscle biopsy). There will then be a 2-week washout period after which the participants will cross over to the other treatment and complete the same 4 testing visits.

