### Objective

The primary aim of this study is to test the hypothesis that 5 days of inorganic nitrate supplementation (16 mmol/day) will improve exercise tolerance (VO_2peak_ and TTE) in both HFpEF and HFrEF patients. We further hypothesize that patients with HFpEF will have larger improvements in exercise tolerance than patients with HFrEF because of greater impairments in their peripheral muscular tissues. The secondary aim of the project is to identify the mechanistic contributors to exercise tolerance in both heart failure classifications via examining the following outcome measures:

Gastrocnemius tissue oxygenation at rest and during submaximal and maximal exercise via near-infrared spectroscopy (NIRS)Vastus lateralis muscle tissue composition and function (angiogenesis, capillaries per unit area and per muscle fiber, mitochondrial function, and muscle fiber composition)Vascular function via brachial artery flow-mediated dilation, lower-limb blood flow via plethysmography, and pulse wave velocity (PWV) and reflection.

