### Vascular Function Visit

Patients will be asked to fast overnight and to abstain from exercise for the 24 hours prior and to avoid caffeine and smoking for the 3 hours before testing. They will also be asked to hold their morning medications until immediately post-testing. All vascular testing will occur following a minimum of 10 min, with the participant in the supine position.

Brachial artery flow-mediated dilation (FMD) will be obtained using a high-resolution Terason ultrasound (LifeHealthcare, New South Whales, Australia) to capture images of the brachial artery. This method has been previously used in clinical populations and has been shown to be reliable [40,59,60]. In brief, FMD will be assessed at baseline, following 5 min of forearm occlusion, and 2 min following occlusion cuff release (reactive hyperemia). These data points will be used to calculate the percentage of change in brachial artery diameter following reactive hyperemia.

Lower limb blood flow will be assessed via venous occlusion strain gauge plethysmography both at rest and during reactive hyperemia following 5 min of occlusion via Hokanson A16 (DE Hokanson, Bellevue, WA), as was previously described [61,62]. Participants will remain in a supine position with their legs elevated (to facilitate venous emptying) for the duration of the test. A cuff will be placed on the upper thigh of the nonbiopsy leg (so as not to put pressure on the biopsy site) to act both as a venous and arterial occlusion cuff while a mercury strain gauge (sized at ~4 cm less than calf width) is affixed around the largest part of the gastrocnemius. For resting measures, the thigh cuff will be inflated to 50 mmHg for 4 to 6 cycles of inflation and deflation to obtain resting blood flow measures. Resting blood flow will be recorded as the average of 3 measurements. Peak hyperemic blood flow will be determined following an ischemic occlusion (pressure set to 30 mmHg above systolic pressure) of the thigh for a period of 5 min. Postocclusion blood flow measurements were obtained every few seconds following cuff release, with the peak value being recorded as the highest value achieved.

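### The NIRS percentage scale is set by a post-cuff response recorded on treatment, so a nitrate effect on that response could shrink, cancel or reverse the nitrate–placebo contrast

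*Protocol article*

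**What the plan says.** The calibration is described in the Protocol article, Maximal Cardiopulmonary Exercise Test Testing Visit. After exercise, a cuff above the knee produces 5 minutes of ischaemia in the leg carrying the NIRS device. The lower anchor is given as "The baseline value for the scale will be the plateau of the oxygenated hemoglobin signal". The upper anchor follows: "whereas the signal response to postcuff release will provide a functional maximum for the normalized scale". The rule covers everything recorded in the test: "All values obtained during the testing will then be expressed as a percentage value within these ranges". Its stated purpose is "to allow for comparisons of the NIRS results to be made between subjects".

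The Abstract (Methods) says that participants "cross over to the other treatment and complete the same 4 testing visits". Study Design and Participants has dosing continue through all four visits of a round. The calibration is therefore performed once on nitrate and once on placebo. No calibration off treatment, and none shared by the two rounds, is mentioned.

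The Background calls nitrate a vasodilatory intervention and cites rat heart failure models with raised muscle blood flow. The Vascular Function Visit includes a closely related leg test, also with 5 minutes of occlusion: "Peak hyperemic blood flow will be determined following an ischemic occlusion". Outcome Measurements lists lower limb blood flow as a secondary outcome. Gastrocnemius oxygenation by NIRS is the first mechanistic measure under the secondary aim (Objective). Statistical Analysis applies to the secondary variables the same kind of analyses as for the primary endpoint: a paired comparison, then a comparison of the two heart failure cohorts.

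**The concern.** A normalised value is a ratio, and it isolates a treatment effect on its numerator only if treatment leaves the denominator alone. Here the denominator is the span up to a reactive-hyperaemia response, recorded while the participant is taking the study drink. The trial elsewhere treats post-occlusion leg hyperaemia as something that nitrate may change. The scaling is justified for comparisons between people, whereas the crossover's main contrast is within a person.

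If the span does move with treatment, a null or negative NIRS result cannot be read as evidence about oxygenation. Statistical Analysis also names tissue perfusion among the factors that may explain changes in exercise tolerance; if NIRS supplies that variable, the distortion carries into those regressions. If the span responds differently in HFpEF and HFrEF, the cohort comparison of change scores is affected as well.

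**Working it through.** The documents state no figure on this point, so there is nothing to reproduce. The check is the algebra of the stated rule.

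**Inputs from the article.** Floor b is the ischaemic plateau and maximum m is the post-release response. Every value x becomes 100·(x − b)/(m − b).

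**Assumptions, not in the documents.** Nitrate multiplies the exercise signal above the floor, (x − b), by (1+h) and the span, (m − b), by (1+g). On placebo the span is 100 units and the exercise value lies 40 units above the floor, that is 40%.

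**Formula.** Normalised value on nitrate ÷ normalised value on placebo = (1+h)/(1+g). The contrast in points is 40·(1+h)/(1+g) − 40.

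**A true rise of 10% (h = 10%).** With an unchanged span the effect is 44 − 40 = +4.0 points.

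| Change in span, g | Nitrate value | Apparent effect (points) |
|---|---|---|
| 0 | 44/100 = 44.0% | +4.0 |
| 5% | 44/105 = 41.9% | +1.9 |
| 10% | 44/110 = 40.0% | 0.0 |
| 15% | 44/115 = 38.3% | −1.7 |
| 20% | 44/120 = 36.7% | −3.3 |

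**No true change (h = 0).** At g = 10% the value is 40/110 = 36.4%, an apparent fall of 3.6 points.

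**General pattern.** For positive h, the effect is attenuated when 0 < g < h, cancelled when g = h and reversed when g > h. Starting from 30% or 60% on placebo changes the number of points but not the pattern.

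**The floor matters too.** Take a raw nitrate value of 44 and a raw maximum of 110, which gives zero effect with the floor at 0. A floor 5 units lower gives (44 + 5)/(110 + 5) = 42.6%, or +2.6 points. A floor 5 units higher gives (44 − 5)/(110 − 5) = 37.1%, or −2.9 points. Both anchors therefore need to be looked at, not only the peak.

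**The case against.** A reader might infer that nitrate is expected to raise the post-release peak and that the normalisation will therefore hide the effect. The documents do not support that. They describe vasodilation and higher muscle blood flow, but nowhere say that the oxygenated haemoglobin peak will rise. The hyperaemia outcome is blood flow by plethysmography, a different quantity from the NIRS signal, so a change in one does not establish a proportional change in the other. The Background also reports that the one cited human study of exercise capacity in HFrEF found no change in any parameter examined. The values of h and g above are invented for illustration; they show what can happen, not what is likely.

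Other limits also stand. A separate range for each round is inferred from the repeated visit, not stated outright. The cuff calibration is described only for the maximal test, not for the submaximal visit. NIRS oxygenation appears under the secondary aim but not in the list of secondary outcomes in Outcome Measurements. Leg blood flow is measured separately, so the perfusion question does not rest on NIRS alone. A condensed article may leave the choice of NIRS scale for the paired test to a fuller document.

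Nor is unscaled change from rest a clean replacement. The resting value is also recorded on treatment, so an equal rise at rest and during exercise would vanish. The secondary aim also asks about oxygenation at rest, where change from rest is zero by construction. The device gives only relative concentrations, and the probe is repositioned between rounds. The choice between scales is a trade-off, which is why the normalisation should stay.

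None of this removes the central point. The article does fix a rule that puts every value from this test over a range measured on treatment, and its stated rationale covers only comparisons between subjects.

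**Conclusion.** The concern holds as a conditional one: if the calibration range responds to nitrate, the nitrate–placebo contrast in normalised NIRS is biased by the factor 1/(1+g), and can be attenuated, cancelled or reversed. Under the illustrative assumptions, a true +4.0 points reads anywhere from +4.0 to −3.3 as g goes from 0 to 20%. Whether g differs from zero cannot be told from the documents, but the trial's own recordings can show it.

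The conclusion rests on the range being measured separately in each round, and on the normalised values entering the paired comparison. The reach is limited to NIRS at the maximal test and to analyses that draw on it for tissue perfusion. VO2peak and time to exhaustion are not touched. This is an inexpensive improvement to interpretation, not a flaw in the trial's main result.

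**What to change.** 1. Keep the normalisation as described.
2. Compare the ischaemic floor, the post-release peak and their span between nitrate and placebo, overall and within HFpEF and HFrEF, and report them with the NIRS results.
3. Pre-specify one sensitivity analysis of the nitrate–placebo contrast that does not depend on each round's treated maximum. Use either one common range per participant across both rounds, or change from same-visit rest in unscaled units. Apply it to the cohort comparison of nitrate change scores as well.
4. State in advance that, if the span differs by treatment, the normalised percentage will not be interpreted as a change in oxygenation.

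The signals needed are already recorded, so the cost is a little more analysis. The sensitivity analysis will carry probe-repositioning noise between rounds. If change from rest is chosen, it cannot address oxygenation at rest, so that part of the secondary aim would need the common range or the normalised values read alongside the anchor comparison.

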### Vascular Function Visit

Patients will be asked to fast overnight and to abstain from exercise for the 24 hours prior and to avoid caffeine and smoking for the 3 hours before testing. They will also be asked to hold their morning medications until immediately post-testing. All vascular testing will occur following a minimum of 10 min, with the participant in the supine position.

Brachial artery flow-mediated dilation (FMD) will be obtained using a high-resolution Terason ultrasound (LifeHealthcare, New South Whales, Australia) to capture images of the brachial artery. This method has been previously used in clinical populations and has been shown to be reliable [40,59,60]. In brief, FMD will be assessed at baseline, following 5 min of forearm occlusion, and 2 min following occlusion cuff release (reactive hyperemia). These data points will be used to calculate the percentage of change in brachial artery diameter following reactive hyperemia.

Lower limb blood flow will be assessed via venous occlusion strain gauge plethysmography both at rest and during reactive hyperemia following 5 min of occlusion via Hokanson A16 (DE Hokanson, Bellevue, WA), as was previously described [61,62]. Participants will remain in a supine position with their legs elevated (to facilitate venous emptying) for the duration of the test. A cuff will be placed on the upper thigh of the nonbiopsy leg (so as not to put pressure on the biopsy site) to act both as a venous and arterial occlusion cuff while a mercury strain gauge (sized at ~4 cm less than calf width) is affixed around the largest part of the gastrocnemius. For resting measures, the thigh cuff will be inflated to 50 mmHg for 4 to 6 cycles of inflation and deflation to obtain resting blood flow measures. Resting blood flow will be recorded as the average of 3 measurements. Peak hyperemic blood flow will be determined following an ischemic occlusion (pressure set to 30 mmHg above systolic pressure) of the thigh for a period of 5 min. Postocclusion blood flow measurements were obtained every few seconds following cuff release, with the peak value being recorded as the highest value achieved.

Vascular stiffness will be assessed by PWV and pulse wave reflection using applanation tonometry via a SphygmoCor XCEL system (AtCor Medical, New South Whales, Australia. The SphygmoCor is a noninvasive diagnostic system that has been used to provide assessments of both the central blood pressure and PWV of clinical patients [63]. For the measurement of pulse wave analysis (PWA), a SphygmoCor arm cuff is placed on the upper arm, aligning the designated markings with the brachial artery. The system then measures pulsations recorded at the brachial artery to produce central aortic pressure waveforms and predict the following: central systolic pressure, central pulse pressure, augmentation pressure, and augmentation index. PWV is measured via a simultaneous comparison of the carotid and femoral arterial pulses. A thigh cuff will be placed around the participant’s upper thigh, which acts to measure the femoral pulse via pulsations, while simultaneously a tonometer will be used to assess the carotid pulse. Higher pulse wave velocities from the carotid to femoral arteries indicate higher aortic stiffness.

### Submaximal Echocardiograph Visit

For this visit, participants will again be asked to refrain from exercise and alcohol for the 24 hours before testing and to abstain from caffeine and smoking for the 3 hours before testing. They will be instructed to follow their normal dietary routine and take their medications. For this visit, participants will complete a series of 3 discontinuous stages (5-min rest in between each stage) of exercise on an echo-compatible recumbent cycle ergometer (Vivid 7 echocardiographic machine, GE, Milwaukee, Wisconsin). At present, the most common measure to assess the heart function during exercise is to have the participant exercise and then capture images immediately after exercise completion. The design of this cycle places the participant in an ideal position to capture echocardiograph images during exercise, allowing for more accurate assessment of cardiac function during exercise. Three independent workloads will be chosen based on participant capacity (Stage 1: 5-20 watts, Stage 2: 15-40 watts, and Stage 3: 30-60 watts). During the exercise test, participants will be fitted with the NIRS device, PhysioFlow, and electrocardiogram, similar to the one used during the max CPX. The echocardiograph will provide measures of CO, stroke volume (SV), mean arterial pressure (MAP), cardiac power output, left-ventricular end-systolic elastance, arterial elastance, preload recruitable stroke work, long-axis contraction and relaxation, mitral flow propagation velocity, and tricuspid incompetence. All echocardiograph assessments will be taken by the same tester to control for intertester variability.

